#### Acquisition of data

Data will be acquired in electronic database and pseudomised. Thereafter, data will be analysed statistically with SPSS. Prior to analysis they will be examined for completeness, accuracy and credibility.

#### Data safety

All databanks will be secured with passwords against unauthorised access. Electronic transmission of any study contents or data will be done with password encryption. The password key, at least eight characters and/or digits through another medium (SMS telephone or post). It shall be changed every other four weeks. Only persons subsidised under number one shall have access to personal data. Uncoded data shall only be seen via Praxis personnel of the medical Praxis of [name] and [name].

## Data analysis

All data that will be quiet for this analysis, shall only serve to answer the main question. No other data shall be acquired analysed for any other purpose. All data shall be acquired and analysed according to GCP, following the declaration of Helsinki and by complying to all EU regulations and the German legislation.

## **6. Number of patients / volunteers**

Five volunteers (+ the inventor) have used the MD. Data from these volunteers shall be analysed.

## **7. Statistics**

This is a retrospective analysis. Most likely, data of some variables will be missing. Data from weight courses/visceral fat from the last 10 years shall be analysed. Most likely only weight courses might be documented. This will only have been done according to clinical necessity. There will be no standardisation regarding time points.

All continuous variables shall be checked for normal distribution with the Kolmogorov-Smirnov test. Data shall be expressed as mean expressed as mean  $\pm$  standard deviation. Normally distributed variables shall be analysed with the two-sided t-test. Not normally distributed variables shall be analysed with the Mann-Whitney-U Test. Comparison of categorical variables shall be generated with the Pearson  $\chi^2$ -test and the Fishers exact test. The linear regression analysis shall be used to identify independent predictors for weight reduction in the follow-up period. Is not expected that these tests shall be used regarding the small number of volunteers. Statistical significance shall be assumed if a null hypothesis can be rejected at  $p \leq 0.05$ . All statistical analysis shall be performed with SPSS 20 ®.

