#### **3.1. What is expected?**

From this analysis of the first volunteers the hypothesis shall be tested that

- there was a continuous increase of weight and of the visceral fat over the last 10 years related to the baseline weight when they splints were first used

- there will be a weight reduction and reduction of the visceral fat and now weight regain, even after stopping using the splints.

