### 3.2. Aim of the study

Primarily the efficacy of the splints shall be proven. The primary endpoint is weight reduction after using the splints. Secondary endpoints regarding mode of action, safety and benefit shall be analysed, if the existing documentation and is sufficient.

Hereafter, the splints shall be standardised regarding the construction and further specified. This will form the basis for the development and certification of the medical device (MD) risk class I and consequent testing in a clinical trial.

It will be the aim of this retrospective analysis of the current observational study to obtain data so that a study protocol can be derived from this including a proof of mechanism for a then certified MD.

A large-scale prospective randomised controlled trial shall be planned to prove the main hypothesis and further to be identified secondary hypotheses to test the splints as medical device.

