#### Baseline values:

- age (in years) and time point 0
- gender
- date of time point 0 and of the earliest documented weight
- weight and waist circumference at time point 0
- height at time point 0
- BMI at time point 0
- categories: BMI > 25, BMI > 30, BMI > 35 .0
- duration of previous attempts to reduce weight
- development of weight and waist circumference over the last years
- number of previous attempts to lose weight
- type of weight reduction programs
- change of medication and inclusion (one month follow-up periods)
- Concomitant diseases
- metabolic syndromes (yes / no)
- Diabetes mellitus (y/n)
- Duration Diabetes mellitus (only in DM patients)
- family history for premature cardiovascular events; m < 55 years , w < 65 years, (y/n)
- current smokers , (y/n)
- hyperlipoproteinaemia (diabetes LDL > 70 mg / dl, non-diabetes> 100 mg /dl OR statin therapy), (y/n)
- art. Hypertension, (y/n)
- number of cardiovascular risk factors (including: family history; m < 55 years , w < 65 years , smoking , hyperlipoproteinaemia (diabetes LDL > 70 mg / dl, non-diabetes> 100 mg /dl OR statin therapy), art. hypertension , Diabetes mellitus)

- orthopaedic problems (y/n)  
type of orthopaedic problem
- social economic status, training, income (rough estimation), status employee, retired

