#### Target variables

- **weight, BMI and waist circumference after using the MD**
- duration of follow-up (in month all years)
- number of follow-up visits
- date of last follow-up visit
  
- Concurrent medication
- change of medication during follow-up (y/n), which?
  
- Laboratory findings:
  - HLP, HBA1C, hs-CRP, BB,
- Sports or physical activity
- adherence of using the MD
- subjective details regarding the MD
- change of eating behaviour
- psychologic statement of the personnel of the medical practice of [name]
- change of quality of life and physical performance

Time point 0 is the visit at which the patient decided to use the MD.

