## **8. Inclusion and exclusion criteria**

### **Inclusion criteria**

1. age: 18 to 95 years
2. gender male and female
3. ability to consent
4. written informed consent
5. exploit of the established evidenced-based options for weight reduction
6. receiving an MD
7. at least two documented visits after receiving the MD

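### One weight at the decision visit anchors both main hypotheses, and no stated analysis uses the earlier weights as each person's own control, so a personal high at time 0 can look like a device effect

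*Protocol*

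**What the plan says.** Section 4 lists the baseline as "weight and waist circumference at time point 0" and defines the anchor: "Time point 0 is the visit at which the patient decided to use the MD". Section 3.1 instead places baseline at first use of the splints, so the protocol holds two definitions.

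Section 3.1 has two expectations. The first is that "there was a continuous increase of weight and of the visceral fat over the last 10 years related to the baseline weight". The second is that "there will be a weight reduction and reduction of the visceral fat and now weight regain, even after stopping using the splints", where the fifth word from the start of the regain clause appears to be a slip for "no". Section 3.2 adds: "The primary endpoint is weight reduction after using the splints". It also says that efficacy is primarily to be proven.

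Section 7 says of the history: "Data from weight courses/visceral fat from the last 10 years shall be analysed". It expects gaps, says weights were taken only on clinical need, and adds: "There will be no standardisation regarding time points". The methods named are a two-sided t-test (paired or unpaired not stated), the Mann-Whitney U test, tests for categorical variables, and a linear regression for predictors of weight reduction in follow-up. It also says these tests are not expected to be used, given the small number of people.

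Section 6 gives five volunteers plus the inventor, with no control group. Inclusion criterion 5 in Section 8 requires "exploit of the established evidenced-based options for weight reduction", and criterion 7 guarantees only two documented visits after receipt of the device.

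**The concern.** Both hypotheses are measured from the same number. If that number is high by chance, or because the person is at the top of a weight cycle, the earlier years look like a gain and the later ones like a loss. One high reading supports both statements at once.

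A high reading is plausible here. Section 2 describes the yo-yo effect and disproportional regain after nearly all programmes, and criterion 5 selects people who have been through such programmes. People may also tend to decide on a new method when their weight is up.

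Without a control group, each person's own history is the only available guide to what would have happened without the device. The history is collected, but nothing in the plan puts it to that use. Section 3.2 makes this analysis the basis for a later trial protocol, so an inflated change would carry into that planning.

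**Working it through.** **No figure to reproduce.** The number of people is simply the number of users. The documents give no within-person SD, correlation or effect size, so every value below for these is an assumption.

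**1. Time 0 as the highest of k recent weights.** Let s be the within-person SD and assume independent weights. The excess at baseline is s × E(max of k standard normals), and E(max) is 0.85, 1.03 and 1.16 for k = 3, 4 and 5.

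| s | k = 3 | k = 4 | k = 5 |
|---|---|---|---|
| 2 kg | 1.7 kg | 2.1 kg | 2.3 kg |
| 3 kg | 2.5 kg | 3.1 kg | 3.5 kg |

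Section 2 quotes 1.5 to 4.5 kg as the result of a daily energy deficit, so the two ranges overlap.

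**2. Time 0 in the upper share q of a person's own fluctuation.** With correlation ρ between weights one year apart, an underlying trend g per year and no device effect, the expected change at one year is −s(1 − ρ)φ(z)/q + g. The factor φ(z)/q is 0.80 for q = 50% and 1.40 for q = 20%.
- s = 2, ρ = 0.5, q = 50%, g = 0: −2 × 0.5 × 0.80 = −0.8 kg.
- s = 4, ρ = 0, q = 20%, g = 0: −4 × 1.40 = −5.6 kg.
- With g = +0.5 kg/year these become −0.3 and −5.1 kg.
- If time 0 is not selected as high, the change is 0 kg (flat trend) or +0.5 kg (rising trend).

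The last line also shows the opposite error. On a true rise of 0.5 kg/year, a device that puts a person 2 kg below their course after one year shows a change of only −1.5 kg.

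**3. Both hypotheses together.** A simulation of the model in step 2 used yearly weights, s = 2 or 4 kg, ρ = 0 or 0.5, g = 0 or 0.5, n = 5 or 6, and 20,000 runs per scenario with no device effect. With time 0 in the upper 50% or 20%, both Section 3.1 statements pointed the hoped-for way in 65% to 99.9% of runs. Without selection they did so in 27% to 42%. This needs no significance test.

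**4. Own history as control.** In the same simulation a straight line was fitted to years −10 to −1 and projected to year +1.
- Time 0 left out: mean false effect 0.0 kg at ρ = 0, and 0.2 to 0.7 kg against the device at ρ = 0.5.
- Time 0 kept in: a false loss of 0.2 to 2.0 kg remains.

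Time 0 must therefore be left out. A prior mean without time 0 can err the other way. If time 0 is the highest of exactly the k weights in hand, the other k − 1 average −E(max)/(k − 1) SD. That is 0.85/2 = 0.43 SD below the true level for k = 3 and 1.16/4 = 0.29 SD for k = 5, or about 0.6 to 0.85 kg at s = 2 kg. The two baselines then bracket the truth.

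**5. Precision.** With ten independent yearly weights (mean year −5.5, sum of squares 82.5) and one follow-up weight at +1, observed minus projected has SD s√(1 + 1/10 + 6.5²/82.5) = 1.27s. For n = 5 the 95% half-width is 2.776 × 1.27s/√5 = 1.58s. That is about 3.2 kg at s = 2 kg and 4.7 kg at s = 3 kg, before any real differences between people.

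**The case against.** The strongest reply is that the history is not ignored. It is listed in Section 4, is to be analysed under Section 7 and has its own hypothesis in Section 3.1, so a before-and-after picture is clearly intended. That is right. A reader might infer that the ten years of weights go unused, and the documents do not support that. What is missing is a defined within-person comparison.

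Second, a reader might infer that a false device effect is bound to appear. That requires time 0 to be a personal high, which no passage states. Criterion 5 says only that established options had been tried. The bias is possible and plausible, but not shown.

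Third, a reader might blame two-sample testing. Only the Mann-Whitney test is clearly for independent groups, and Section 7 does not expect the tests to be used. This stands, and it moves the risk to the reading of a descriptive fall. It does not remove the risk, because the bias lies in the mean change itself.

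Fourth, exclusion criterion 1 removes people with a recent loss of at least 5% but has no counterpart for recent gain. This might seem to push the baseline up materially. Simulated with no other selection, for weights of 80 to 100 kg and correlations of 0 to 0.5, it adds 0.02 to 0.23 kg at SD 2 kg and 0.16 to 0.65 kg at SD 3 kg. It is also a reasonable guard against crediting an earlier loss to the device. It does not carry the point.

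Last, the model for irregular weights may sit in an analysis plan that is not shown. That is fair for the modelling detail. The single-weight baseline and its role in both hypotheses are fixed in the protocol.

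**Conclusion.** The point holds in conditional form. The protocol fixes one weight at the decision visit as the reference for both the earlier rise and the later fall, defines that visit in two ways, and aims to prove efficacy in five or six people without controls and without a stated own-control comparison. A high time-0 weight can therefore produce an apparent effect.

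Under the highest-of-3-to-5 assumption with independent weights, the size is 1.7 to 2.3 kg at SD 2 kg and 2.5 to 3.5 kg at SD 3 kg. It shrinks with serial correlation and vanishes if time 0 is not a peak. If weight was truly rising, the simple change from time 0 understates any benefit. The documents cannot say which case applies, and that is the reason to report more than one reference. The change should be made. It is not evidence that any result already obtained is wrong.

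**What to change.** In Sections 3.1, 4 and 7:

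1. Use one definition of time 0 throughout.
2. Plot every person's dated weights before and after first use.
3. Beside the change from time 0, report each person's change from the mean of the weights recorded in the 12 months before time 0, excluding the time-0 weight. State how many weights contribute.
4. Where a person has enough earlier weights, with the minimum number set in advance, fit a line to the pre-device weights without time 0 and project it to the follow-up dates. Report observed minus projected weight per person, with the mean and a t-based 95% confidence interval.
5. State that if these results disagree, the fall from time 0 will not be described as proof of efficacy.

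Separate post-device slopes are not advised, because only two post-device visits are guaranteed. With ten yearly earlier weights, two visits within a year and SD 2 to 3 kg, the difference in slopes has an SD of about 2.3 to 3.5 kg/year per person. With n = 5 that gives a half-width of about 2.9 to 4.3 kg/year.

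The cost is a little more analysis of data already being extracted. Some people will not contribute to items 3 or 4, because weights are sparse and irregular, and intervals will be wide. A straight line does not model cycling, and concurrent lifestyle change is not removed. The headline change may be smaller.

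### Section 7 names only mean ± SD and independent-observation methods for irregular serial weights, and no rule gives one follow-up value or one pre-use slope per user

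*Protocol*

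**What the plan says.** Section 7 sets the material to be analysed: "Data from weight courses/visceral fat from the last 10 years shall be analysed". On how the weights came to be recorded it says "This will only have been done according to clinical necessity" and "There will be no standardisation regarding time points".

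It then names the methods. Data are to be expressed as mean ± SD. For tests: "Normally distributed variables shall be analysed with the two-sided t-test" and "Not normally distributed variables shall be analysed with the Mann-Whitney-U Test". For predictors: "The linear regression analysis shall be used to identify independent predictors for weight reduction in the follow-up period". It adds that, given the small number of volunteers, these tests are not expected to be used.

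Section 6 gives the number of people: "Five volunteers (+ the inventor) have used the MD". Section 4 fixes one baseline weight per user, at time point 0, which is a single visit. The target is only the weight after using the device. Section 8 requires at least two documented visits after receiving the device and sets no maximum. Section 3.1 asks whether weight rose continuously over the ten years before use, and Section 3.2 makes weight reduction the primary endpoint.

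**The concern.** A weight course is several correlated measurements on one person, and here their number and timing differ between people. Mann-Whitney U compares two independent samples. A t-test not specified as paired, and ordinary linear regression, also take each value as an independent observation. No paired or repeated-measures method is named.

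The step that would make these tools usable, one value per user, is missing in two places:

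- **After use.** Each user has at least two follow-up visits, and nothing says which one supplies the follow-up weight.
- **Before use.** A continuous rise over ten years cannot be judged from a single weight, so the series has to enter the analysis. No slope or other per-user summary is defined.

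With five or six people who probably differ more from each other than each does over time, a change in who contributes weights can look like a change in weight. Weighing by clinical need makes it plausible that the number of weighings is related to a user's health or weight. Section 3.2 wants efficacy proven and the results used for device development and a later trial protocol, so such an artefact would be carried forward.

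**Working it through.** The protocol gives no sample-size calculation, SD, effect size or weighing counts, so there is no stated figure to reproduce. Only the number of users (5 or 6), the 0.05 level and the comparison value of 1.5 to 4.5 kg (Section 2, on evidence-based programs) come from the document. Every other input below is an assumption.

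**1. Mechanism, by hand.** If all weighings are pooled, the mean is Σ(nᵢ·wᵢ)/Σnᵢ, where wᵢ is user i's weight and nᵢ the number of weighings. Take five users constant at 85, 90, 95, 105 and 125 kg, weighed 2, 3, 4, 6 and 10 times before and 10, 6, 4, 3 and 2 times after.

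- Before: (2×85 + 3×90 + 4×95 + 6×105 + 10×125)/25 = 2700/25 = 108.0 kg
- After: (10×85 + 6×90 + 4×95 + 3×105 + 2×125)/25 = 2335/25 = 93.4 kg
- Apparent change: 93.4 − 108.0 = −14.6 kg. The true change in every user is 0 kg.

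These counts are deliberately reversed against body weight. They show that the artefact is possible, not how large it is likely to be. If each user's share of the weighings is the same before and after, there is no artefact. If each weight is first expressed as a change from that user's own time point 0, this example gives exactly 0 kg.

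**2. Size when counts are unrelated to weight.** Simulation with no true change, mean 95 kg, counts drawn at random per user, and a two-sample t-test on all weighings at p ≤ 0.05:

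| Weighings per user, before / after | Between-user SD | Within-user SD | Null rejection, pooled t-test | Pooled fall ≥ 4.5 kg |
|---|---|---|---|---|
| 1–20 / 2–12 | 12–18 kg | 2 kg | about 19–22% | about 8–19% |
| 3–20 / 2–10 | 10–20 kg | 1.5 kg | about 12–14% | about 6–15% (SD 12–18 kg) |
| 5–10 / 5–10 | 12–18 kg | 2 kg | below 0.3% | about 0.6–3% |

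The error runs in both directions. With very unequal counts the test rejects too often. With similar counts it rejects far below 5%, because the between-user spread inflates the error term.

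**3. One change per user.** In the 3–20 / 2–10 setting, a one-sample t-test on each user's own change rejects in 4.3% to 4.9% of null runs, with 5 or 6 users.

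**4. One before and one after value per user.** The pooling artefact is then gone, but an independent-samples test still does not fit. Assuming a true loss of 5 kg, SD of change 3 kg and between-user SD 10 to 20 kg, the unpaired t-test and Mann-Whitney U detect the loss in about 0.1% to 2.3% of runs. The paired t-test does so in about 79% (n = 5) to 90% (n = 6).

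**The case against.** A reader might infer that the plan does weight each user by visit count. The documents do not support that: no section says that individual weighings are entered as observations. Several items point to a per-user reading. The baseline is one weight at one visit, Section 3.1 relates the course to the baseline weight, and both the primary endpoint and the regression outcome are a weight reduction, which is a change. The listed "number of follow-up visits" is one descriptor per person and is no evidence of pooling. All of this stands, and it makes the point conditional. It does not supply the missing rule for the follow-up value or the pre-use slope.

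A reader might also infer that the trial will report false significance in about 20% of cases. That does not follow. The figure depends on assumed counts and falls below 1% under others, and the protocol does not expect the tests to be used. The p-value argument is therefore secondary. What remains exposed is mean ± SD, which a pooled summary distorts in the same way.

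Finally, the exact summary or longitudinal model could sit in an analysis plan that is not shown. That is fair for the details. But Section 7 itself chooses the methods, and the chosen methods do not match the data described beside them.

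**Conclusion.** The point holds in conditional form. Section 7 pairs irregular serial weights with mean ± SD and methods for independent observations, and no section gives one follow-up value or one pre-use slope per user. If the recorded weights are entered directly, users count by number of weighings, the mean can move with no individual change, and any p-value is miscalibrated.

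The size cannot be derived from the documents. Under the assumed counts and SDs, null rejection by a pooled t-test ranges from under 1% to about 20%, and a spurious fall of at least 4.5 kg, the upper end of the range that Section 2 gives for an energy-deficit diet, from under 1% to about 19%. The main practical exposure is the descriptive summary. The correction should be made, because it is cheap and removes the ambiguity.

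**What to change.** In Section 7:

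1. State that the user is the unit of analysis.
2. Show each user's full weight course.
3. Compute per user one weight change from time point 0 to a follow-up visit fixed in advance, for example the last, and one pre-use slope in kg/year.
4. Summarise these 5 or 6 values per measure, not the individual weighings.
5. If any test is used, apply a within-user method (paired or one-sample) in place of Mann-Whitney U or a t-test on the weighings. With 5 users the exact signed-rank test cannot go below two-sided p = 2/2⁵ = 0.0625; with 6 its minimum is 2/2⁶ = 0.031.

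A mixed model with random intercept and slope is not recommended. With 5 or 6 users it is fragile: in 150 simulated five-user datasets (assumed intercept SD 15 kg, slope SD 0.5 kg/year), about 63% of fits gave a warning or failed to converge.

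The cost is a few sentences, slightly more analysis work and no new data. The apparent sample size becomes 5 or 6, so results will look less precise.

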## **Evidence-based intervention programs**

Overweight and obesity can be prevented through environmental and community measurements. For weight reduction and to stabilise reduced weight, basic measures like teachings, behavioural changes, physical activity and healthy eating with a deficit in energy form the basis in evidence-based weight reduction programs. The advantages of weight reduction, even by 10%, regarding mortality, general health and obesity-associated diseases are well documented. Weight reductions result in improvements of diabetes mellitus 2, hyperlipidaemia, arterial hypertension, cardiovascular risk profile and ovary function, furthermore of reduced breathlessness, improvement of quality of sleep, sleep apnoea, back and joined pain, as well as osteoarthritis and psychosocial components.

Regardless of the composition of the diet a daily deficit of energy of around 500 cal per day results in a weight reduction of around 1.5 to 4.5 kg over a longer period. Cost-effective is defined as measures is for weight reduction that costs less than US\$50,000 / DALY. This is the case for all state and societal programs as well as for most diets and behavioural changes.

The high percentage of quitters (45%) of programs and the so-called yo-yo effect with weight regain after nearly all programs are highly problematic. Current prevention therapies are characterised by a disproportional weight regain after interventions. This is especially the case for elderly patients that are not used to weight reduction programs including sufficient physical activity. This leads to constant weight gain with increasing age of the community and the individual.

Factors that influence the quantity of food include the quantity and variety of the food offered, visual and anticipatory stimuli and other behavioural patterns as well as satiety. Satiety is a complex process that is mediated by diverse short, middle and long acting mediators in the hypothalamus. Different brain areas integrate these complex neuronal and hormonal signals and thus influence food intake and other behavioural patterns or the emotional state.

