### **3. Hypothesis**

The aim is to test the main hypothesis that using the Genustrainers will lead to a persistent weight reduction.

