## **9. Data privacy protection**

All analysis that goes beyond clinically indicated and Sämtliche Auswertungen über die klinische indizierten und all investigations in humans are subject to the current legislation, rules and directives, the ethical guidelines of the World Medical Association from 1996, the Germans medical associations professional code of conduct as well as the Data Protection Act.

Patients shall be asked prior to the analysis via telephone about their consent to participate. In case of agreement they shall be provided with a consent form. Only after receiving the informed consent shall the data be analysed.

All analysis shall be performed pseudomised with the code that consists of characters and digits. Only the practitioner and the assisting personnel shall have access to the original data from where the patients may be re-identified.

Electronic databases shall only be transmitted encrypted. The code, consisting of a combination of at least eight characters and digits shall always be communicated through another medium.

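### For practice patients, regain after the last recorded weight cannot appear in the data, although absence of regain is the hypothesis and the planned consent call could supply a current weight

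*Protocol*

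**What the plan says.** Section 3 of the protocol states the main hypothesis that "using the Genustrainers will lead to a persistent weight reduction". Section 3.1 extends it to the period after use ends: "now weight regain, even after stopping using the splints", where *now* reads as a misprint of *no*. Section 3.2 adds: "The primary endpoint is weight reduction after using the splints", without a time point.

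Section 7 describes how the weight courses of the last 10 years came to be recorded: "This will only have been done according to clinical necessity". It continues: "There will be no standardisation regarding time points". The target variables in section 4 include the duration of follow-up, the number of visits and the "date of last follow-up visit".

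Under Origin of data in section 5, data are taken from patient records. Only volunteers who are not patients of the practice have data obtained by telephone and from material they supply.

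Section 9 provides a contact before the analysis: "Patients shall be asked prior to the analysis via telephone about their consent to participate". Nothing there, in section 5 or in section 7 says that a current weight is asked for. Section 8, inclusion criterion 7, admits only users with two or more recorded visits once they have the device. Section 6 gives the number of users as five plus the inventor.

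**The concern.** A claim of persistence needs a weight late enough to show regain if it happened. For practice patients, the plan has only the weights that clinical attendance happened to produce. When attendance ends, observation ends, and whatever the weight does afterwards is outside the data. This matters most for the second part of the hypothesis, the period after the splints are stopped, because reasons to visit the practice may also lapse then.

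The protocol's own background gives cause for care: "The high percentage of quitters (45%) of programs and the so-called yo-yo effect with weight regain after nearly all programs are highly problematic". If regain and non-attendance go together among splint users, the recorded weights look more favourable than the users' current weights, and no averaging of recorded weights corrects that. Section 3.2 intends these data to shape the protocol of a later randomised trial, so an overstated impression of persistence could carry into its planning.

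**Working it through.** The protocol states no effect size, power or sample-size calculation for this study, so there is no figure to reproduce. The check has two parts.

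**What the plan can observe**

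| Needed for the hypothesis | What the protocol provides for practice patients |
|---|---|
| A weight late after the start of use (section 3) | Whatever weights clinical need produced (section 7) |
| A weight after use has stopped (section 3.1) | No provision |
| A comparable time of assessment across users | No standard time points (section 7); none given for the endpoint (section 3.2) |
| A way to reach users who no longer attend | A telephone call for consent (section 9), not used to obtain a weight |

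The first three rows show the gap. The fourth shows that a means of closing it is already in the plan.

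**How much unseen regain could matter (illustration only)**

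Inputs:
- *n* = 5 users, or 6 with the inventor (section 6).
- *L* = 1.5 to 4.5 kg recorded mean loss. Section 2 gives this range for a dietary energy deficit; it is borrowed here as an order of magnitude.
- *k* = number of users who regain everything after their last recorded weight. This is an assumption, shown for *k* = 1 and 2. It cannot exceed the number of users who are practice patients, which the protocol does not state.

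Assume that every user has recorded loss *L* and that *k* of them have since returned to baseline unseen. Then

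- recorded mean = *L*
- current mean = *L* × (1 − *k*/*n*)
- ratio of recorded to current = 1 / (1 − *k*/*n*)

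| *n* | *k* | *L* = 1.5 kg becomes | *L* = 4.5 kg becomes | Ratio |
|---|---|---|---|---|
| 5 | 1 | 1.5 × 0.80 = 1.2 kg | 4.5 × 0.80 = 3.6 kg | 1.25 |
| 5 | 2 | 1.5 × 0.60 = 0.9 kg | 4.5 × 0.60 = 2.7 kg | 1.67 |
| 6 | 1 | 1.5 × 5/6 = 1.25 kg | 4.5 × 5/6 = 3.75 kg | 1.20 |
| 6 | 2 | 1.5 × 4/6 = 1.0 kg | 4.5 × 4/6 = 3.0 kg | 1.50 |

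Partial regain scales the difference down. With *n* = 5, *k* = 1 and half the loss regained, 4.5 kg becomes 4.5 × (1 − 0.5/5) = 4.05 kg.

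The error can also run the other way. Suppose one of five users was last weighed at baseline because of a clinical problem and has since lost 4.5 kg, like the other four. The recorded mean is then (4 × 4.5 + 0)/5 = 3.6 kg against a current 4.5 kg.

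**The case against.** Several counter-arguments are sound and limit the point.

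- **No last-weight rule exists.** A reader might infer that a user who regained and left is represented by the last, low weight. The protocol does not say so. It names neither that rule nor any other, the last recorded weight need not be the lowest, and the choice among recorded weights may properly sit in an analysis plan that is not shown. What remains is that no such choice can reach a weight that was never taken.
- **Not every user is affected.** Section 5 gives volunteers outside the practice a telephone route. The gap concerns practice patients.
- **The direction is not established.** A visit prompted by clinical need may happen because weight or a related condition has worsened. Bias towards the hypothesis is plausible, but the documents do not show it.
- **The 45% does not transfer.** It is tempting to apply the quit rate in section 2 and put the overstatement at 0.45 × 1.5 = 0.68 kg to 0.45 × 4.5 = 2.03 kg. That rate describes other programmes, and the step assumes that every quitter regained everything unseen. Some early leavers would also be removed by inclusion criterion 7 or by the exclusion for reduced compliance, rather than counted at a low weight. That is a separate selection on attendance.
- **The limitation is partly disclosed.** Section 7 admits irregular recording and missing data, does not expect the formal tests to be used, and covers the years before the splints as well as follow-up. Section 3.2 leaves proof of the main hypothesis to a later randomised trial. Disclosure does not supply the missing weight, but these facts keep the point modest.
- **A new weight changes a retrospective design.** This is true, and it is a real cost. Under Data analysis, section 5 limits data to what answers the main question, and a closing weight does that.

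**Conclusion.** The point holds in a limited form. For practice patients, a plan followed exactly as written cannot detect regain after the last recorded weight, although absence of regain is what sections 3 and 3.1 set out to show. This rests on the text alone and needs no numerical assumption.

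The size is unknown. If users who regain tend to stop attending, each unseen full regainer among five removes one fifth of a common recorded loss. That figure assumes equal recorded losses and complete regain, and it says nothing about what happened to these users. The finding is a worthwhile and inexpensive improvement. It does not show that the recorded results are wrong.

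**What to change.** 1. In section 5 (Origin of data), in section 9 and in the consent form, add that at the existing consent contact each user is asked for one dated current weight. Mark it as scale-measured (at the practice or by the user's own doctor) or self-reported, and label it as obtained prospectively.
2. Report it as a closing weight alongside the record-based result, not in place of it.
3. For each user, report the time from the last recorded weight to data extraction. Section 4 already collects the date of the last visit, which may differ from the date of the last weight.
4. Where no recent weight can be obtained, add a sensitivity analysis that counts that user at the time point 0 weight. Fix what counts as recent before extraction. Describe the result as a sensitivity scenario and not as a worst case, because section 2 itself describes regain as disproportionate.

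The cost is one added item at a contact already planned, for at most six people, with matching consent wording. The study gains a small prospective element, so its description as retrospective in section 5 needs a qualifier. Self-reported weights carry their own error, which is why the source should be recorded.
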